## Abstract

**Background:**

Homelessness is a national crisis in the United States, particularly in the veteran population. Due to multiple chronic conditions, homeless individuals have elevated risk for acute care service use. Engagement in primary and specialty care can mitigate this risk. Interventions grounded in evidence-based practices of peer support, patient-centered care, and whole health are effective for increasing service engagement. However, implementation of such interventions with high-acuity patients often requires multi-component strategies that are intensive and costly. This protocol paper describes a hybrid type 3 effectiveness-implementation trial of Employing Peer Outreach and Whole Health in Recovery (EMPOWER) with high-need, homeless-experienced veterans in permanent supportive housing and will evaluate the impact and cost of high-intensity (vs. low-intensity) implementation strategies on outcomes.

**Methods:**

(Aim 1) At 7 sites in the Veterans Health Administration (VA), a mixed methods pre-implementation evaluation will identify determinants and their potential impact on uptake of EMPOWER and inform modifications to the intervention and implementation strategies as needed. (Aim 2) A staircase cluster randomized design will evaluate the rollout of the implementation strategies, beginning with Audit and Feedback (low-intensity) and then switching to Implementation Facilitation (high-intensity) after 6 months. Implementation Facilitation is hypothesized to have a greater impact on the reach, effectiveness, adoption, implementation (fidelity), and maintenance of EMPOWER. (Aim 3) A budget impact analysis will estimate the average cost of implementing EMPOWER at future sites and comparative costs for implementing the low- and high-intensity strategies.

**Discussion:**

This project will provide information on the relative impacts and relative costs of strategies aimed at implementing a peer-led, patient-centered, whole health intervention for homeless-experienced veterans in permanent supportive housing. The findings will provide guidance to VA and other healthcare systems that serve the aging population of homeless-experienced veterans.

**Trial registration:**

Clinicaltrials.gov (NCT07309224).

Contributions to the literature
High-quality care for homeless adults includes peer-based, holistic approaches. Such interventions are challenging to implement in care systems though because they require multi-pronged strategies that are costly.This project will evaluate the benefits and costs of using high- and low-intensity implementation strategies to increase uptake of an intervention that employs peer outreach and whole health to increase homeless-experienced veterans’ care engagement.Since homeless veterans in the United States utilize both Veterans Affairs and community-based care, knowledge of what works for implementing high-quality care and the associated costs are critical for public-health systems that provide a safety-net for this vulnerable population.

## Background

Homelessness is a national crisis in the United States (US). As of 2024, 23 out of every 10,000 individuals in the US is either unsheltered or unstably housed on any given night and rates of homelessness have increased in recent years [1]. Approximately 2 of 3 homeless individuals has a mental health disorder, with rates highest for substance use disorders (SUD) [2]. The relationship between homelessness and mental illness is complex and bidirectional – mental illness both increases the risk for homelessness, and mental health can be further exacerbated by the stress and sequalae of housing instability [3]. Consequently, homelessness is a robust predictor of utilization of acute care services, such as hospitalizations and emergency department visits, particularly in the veteran population [4, 5]. For these reasons, various national policies and initiatives emphasize the importance of increasing homeless individuals’ access and engagement to both primary care as well as specialty care for SUD and mental health [6].

The most effective interventions for increasing engagement in outpatient services and reducing overuse of acute care among homeless adults leverage data analytics to target and tailor services to the highest-need patients [7, 8], employ peers to help build trust and reduce stigma [9], use a holistic (vs. disease-focused) approach to incorporate patient preferences and goals [8, 10], and emphasize care coordination across an interdisciplinary team [11]. These elements form the basis of Employing Peer Outreach and Whole Health in Recovery (EMPOWER) – a multicomponent intervention to facilitate homeless-experienced veterans’ (HEVs) access and engagement in primary care and specialty care services [12, 13].

EMPOWER was developed in partnership with leaders from the Veterans Health Administration’s (VA) Homeless Program Office and is founded on three evidence-based practices (EBP): (1) peer support, (2) patient-centered care, and (3) Whole Health. Peer specialists (“peers”) are individuals with lived experience of substance use and/or mental health problems who are now in recovery and trained to support those who are actively struggling with these problems. Multiple RCTs and meta-analyses have found peer support to have a positive impact on self-reported recovery and empowerment, engagement and retention in substance use and mental health treatment, and housing stability [14, 15]. Patient-centered care is regarded by the National Academy of Medicine as foundational to effective care for high-need patients [16]. In three RCTs, peer-led, patient-centered interventions for low-income veterans with chronic health conditions increased engagement in primary care, reduced hospitalizations, and yielded a positive return on investment [17]. VA is a national leader in the implementation of Whole Health – a patient-centered care approach that focuses on empowering patients to pursue wellness in service of their life goals and values [18]. An 18-site evaluation in VA found that patients with chronic pain and mental health who received Whole Health (vs. conventional care) services had significantly greater decreases in opioid use, pain, and stress, and increases in care engagement [19].

### Barriers to implementing EBPs with vulnerable populations

An inherent challenge to implementing EBPs such as EMPOWER with vulnerable populations are the complex care needs of these patients [20]. For example, HEVs tend to have multiple, chronic physical and behavioral health conditions, along with numerous psychosocial needs (e.g., food insecurity, lack of transportation, limited digital access and literacy), which limit these patients’ capacity and motivation for self-care, goal-setting, and care engagement [21, 22]. Further, by virtue of both their level of need and eligibility for benefits, HEVs are frequently served by multiple healthcare systems and social services that are poorly integrated, leading to care fragmentation [23]. As a consequence, EBPs for high-need HEVs tend be intensive, multi-component, and require coordination across multiple stakeholders [24].

Peers may help to mitigate some of the challenges to implementing EBPs with vulnerable populations. Through their ability to build trust, role-model self-care, and provide community outreach, peers are uniquely suited to facilitating HEVs’ engagement in self-care and professional care [9]. Peers can also assist with care navigation and linkage to resources across the diverse set of services and systems available to HEVs. Successful implementation of peer-delivered EBPs, however, is dependent on several determinants such as leadership support and engagement, education and training, regular supervision, and clarity regarding the peer role [25, 26].

### Strategies to support implementation of EBPs with vulnerable populations

Education and training are generally insufficient to support the implementation of complex, multi-component interventions such as EMPOWER [27]. Implementation research on interventions similar to EMPOWER have highlighted the importance of monitoring fidelity metrics [28]. Audit and Feedback reports are an evidence-based approach to such monitoring as they include providing key stakeholders at intervention sites with summarized data about their performance relative to a standard or benchmark. This strategy is rooted in behavioral science and the belief that feedback can foster awareness of performance gaps and, in turn, motivate individuals to change their behavior to achieve desired outcomes (e.g., adoption and sustainment of an intervention) [29].

Notwithstanding the potential benefits of Audit and Feedback, more intensive strategies may be needed to further enhance implementation of complex EBPs that serve high-acuity populations [27]. One example, Implementation Facilitation [30], is a collaborative strategy in which trained individuals work with organizations or teams to support the adoption, implementation, and sustainment of an EBP. It is a dynamic process that involves tailored guidance, problem-solving, technical assistance, and capacity-building activities to address specific barriers and leverage facilitators of change [31]. To this end, external facilitators often collaborate with local champions and/or internal facilitators to bring expertise regarding the implementation processes and have transferable knowledge in relevant clinical and behavior change models that inform implementation of the EBP. For example, external facilitation in the form of pre- and post-implementation site visits, regular calls, and interactive support of performance data was shown to be effective for the implementation of peer services in multidisciplinary teams in VA [32].

### Objectives and aims

In this paper, we describe the protocol for a multi-site trial to evaluate the implementation of EMPOWER with high-need, HEVs in the Housing and Urban Development (HUD) and VA Supportive Housing (VASH) program. HUD-VASH is the largest permanent supportive housing program in the US, housing over 180,000 veterans since fiscal year 2012. HUD-VASH has two goals: (a) assist HEVs with obtaining permanent supportive housing, and (b) facilitate access to healthcare and psychosocial services for veterans to maintain housing [33]. The overarching objectives of the current trial are to implement and evaluate EMPOWER at 7 VA sites by (Aim 1) identifying pre-implementation barriers and facilitators to make fidelity-consistent modifications to the intervention and to refine implementation strategies for the local settings; (Aim 2) using a hybrid type 3 staircase cluster randomized trial to test the implementation of EMPOWER through tailored low-intensity (Audit and Feedback) and high-intensity strategies (Implementation Facilitation); and (Aim 3) conducting a multi-payer economic analysis. Implementation outcomes will be evaluated using the Reach, Effectiveness, Adoption, Implementation, and Maintenance (RE-AIM) framework [34]. We hypothesize that the high-intensity implementation strategy of Implementation Facilitation will have a greater impact on all RE-AIM outcomes than the lower-intensity strategy of Audit and Feedback.

Figure 1 provides the implementation logic research model [35], which guided the planning of the current trial. Examples of key determinants are provided, which informed the selection of the implementation strategies to be tested. The determinants were identified from the aforementioned literature, with relevant domains from the Consolidated Framework for Implementation Research (CFIR) [36] and the Dynamic Sustainability Framework (DSF) [37] determined from a scoping review of implementation studies in vulnerable populations [38]. For example, leadership engagement (CFIR: Inner Setting) is a critical determinant of successful implementation of peer-delivered EBPs as well as health-focused interventions for vulnerable populations [26], suggesting that meeting with local opinion leaders will be a key activity in the design of the Implementation Facilitation strategy in the current trial. The model also specifies how the RE-AIM outcomes will be measured and the hypothesized mechanisms of how the implementation strategies will impact those outcomes.

**Fig. 1 Fig1:**
[figure not shown]
Implementation research logic model for EMPOWER in HUD-VASH programs

## Methods

### Aim 1

To refine the implementation approach of EMPOWER at project sites, a convergent parallel mixed methods pre-implementation evaluation will be conducted to identify a local understanding of key determinants and their potential impact on uptake of the intervention [39]. The design of this evaluation is guided by CFIR and DSF [40]. An integration of these two frameworks was previously applied in a mixed methods, multi-site trial to identify determinants to implementation of an EBP for HEVs in the HUD-VASH program [40]. At each site, we will conduct qualitative interviews with 5–10 key informants – e.g., HUD-VASH case managers, peers, and supervisors. Interviews will be conducted via Microsoft Teams, audio-recorded with permission, and follow a semi-structured interview guide. De-identified audio-files of all interviews will be transcribed and analyzed using a rapid qualitative approach, which has been found to yield equivalent findings to more in-depth, time-intensive methods [41]. These analyses will be guided by the Planning for and Assessing Rigor in Rapid Qualitative Analysis (PARRQA) framework, which provides criteria to ensure rigorous planning, conduct and evaluation of qualitative data (e.g., summary template development, matrix analysis) [42].

To complement the qualitative data, the key informants will also be asked to complete three measures of acceptability, appropriateness, and feasibility of the proposed intervention. Each measure consists of four items. The Acceptability of Implementation Measure will measure the extent to which the key informants perceive EMPOWER to be agreeable or satisfactory [43]. The Intervention Appropriateness Measure will be used to assess the perceived fit, relevance, and compatibility of EMPOWER with the practice settings [43]. The Feasibility of Intervention Measure will measure the extent to which EMPOWER can be successfully implemented within the settings [43].

### Aim 2

#### Design

We will conduct an adaptation of the multi-site hybrid type 3 cluster randomized staircase stepped-wedge trial, evaluating the implementation of EMPOWER while gathering data on its effectiveness. The staircase design is an adaptation to stepped wedge designs (SWD) that accommodate more flexible implementation (i.e., less burden to sites and clinicians). At the same time, it offers robust statistical efficiency given that statistical information is often strongest around time periods in the SWD when switching from one implementation strategy to another [44]. For EMPOWER, of interest is the effect of switching from Low Intensity (LI) to High Intensity (HI) implementation strategies. An imbalanced design [45] will be employed in which sites will spend twice as long in HI than LI (see Fig. 2). The use of an imbalanced design further accommodates the anticipated needs of sites to be enrolled in EMPOWER.

**Fig. 2 Fig2:**
[figure not shown]
Staircase cluster randomized trial analytic approach

#### Sample

At each implementation site, eligible patients will be identified from VA’s Homeless Registry “Hot Spot” reports, which use real-time data on acute care service utilization to identify high-need, housing-insecure patients [7, 46]. These reports identify veterans on the VA Homeless Registry (i.e., those who had received VA housing services in the past two years) who had ≥ 1 hospital admissions and/or ≥ 2 ED visits in the past quarter of the fiscal year [47]. Reports are housed on VA’s Support Services Center (VSSC) website with data primarily drawn from the Corporate Data Warehouse (CDW). Data for the reports are updated nightly and separate reports are generated for those who are (and are not) enrolled in VA primary care. From these reports, we will identify patients at each implementation site who are (a) currently enrolled in HUD-VASH, (b) have a mental health and/or SUD diagnosis, and (c) have not been engaged in either primary care or mental health during the quarter that they were flagged on the report. Approximately 585 patients across the target sites are estimated to be eligible to receive EMPOWER during the project period.

Power was assessed by testing a total of 448,560 plausible scenarios for a binomial outcome (e.g., patient reach) with the effect size (θ) of central interest being the mean difference in proportion of patients reached when moving from LI to HI. We assessed the necessary number of patients to achieve Power = 0.80 at α = 0.05, by including a random intercept for each cluster in the analyses (τ) is ∈ {0.01, 0.05, 0.10, 0.15} with θ ranging from 0.01 to 0.20 increase in number of patients reached and an autoregressive correlation of 0.7 between LI and HI implementation periods. Under a variety of plausible scenarios, we assessed power in relation to sample sizes ranging from a total N of 200–1000 patients (the plausible lower and upper limits, respectively, of patients eligible for EMPOWER). We observed Power = 0.80 to be achieved in sample size ranges between 227 and 278 patients.

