#### Outcome measurement

The RE-AIM framework [34] will be used evaluate the implementation of EMPOWER. Reach will be measured in terms of the number of patients who are willing to receive EMPOWER, out of all patients that are estimated to be eligible at potential sites. Effectiveness will be operationalized as number of outpatient visits in primary and specialty visits for mental health/SUD care, engagement in Whole Health services offered by sites [50], and premature exits from the HUD-VASH program. Additional patient-level outcomes will include rates of suicide screening and hospitalizations and emergency department visits, particularly for mental health or substance use. All service use variables will be measured in terms of receipt in VA and in the community using data from CDW. Adoption will be measured in terms of the number of peers in HUD-VASH at sites that are trained in EMPOWER and initiate the intervention with eligible patients at their site. Implementation will be operationalized in terms of fidelity to the various elements of EMPOWER at the site level, as measured via activity logs embedded in the EHR and electronic data capture logs (e.g., Qualtrics) to document type and length of encounters. Maintenance will be measured by the number of patients who are continuing to engage in EMPOWER and other VA services over the duration of the intervention (i.e., 6 months). To supplement the quantitative data used to operationalize the RE-AIM domains, we will conduct semi-structured qualitative interviews by phone with six key informants at each site – e.g., HUD-VASH peers, supervisors, and case managers (n = 36). The interview questions and format will be aligned with the qualitative data collection methods described above in Aim 1.

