#### Analysis

We hypothesize the HI (vs. LI) implementation strategy will have a greater impact on the RE-AIM outcomes*.*For each outcome, we will specify Generalized Linear Mixed Effects models (GLMMs) using unstructured correlation matrices for random effects to flexibly account for variation over time within patients and variation over time within cluster sites with patients clustered within sites [51]. Individual patients may be observed in both LI and HI (thus unbalanced within clusters over time, with some observed multiple times and others at only one stage of implementation). Random effects components of the GLMM will account for this unbalanced panel nature of patient eligibility and site volume in any given time point [51]. In addition to the staircase design’s randomization providing some protection from confounding influences, we will include both patient- and site-level covariates to improve efficiency of the treatment estimates. At the patient level, we will account for demographics to explore potential variations in effectiveness based on these factors (interaction terms). At the site level, we will account for covariates that may represent confounders despite randomization, including site patient volume normalized by providers at the site (site capacity and time to meet patient needs) and staffing changes. Communication with the sites will enable us to identify other factors affecting implementation that we may want to account for in models that may affect the relative success of HI over LI, or vice versa.

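### Service-use outcomes count the same events that select patients, and LI always precedes HI, so the HI-versus-LI contrast is exposed to regression to the mean in favour of HI

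*Protocol article*

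**What the plan says.** All references are to the Protocol article, Aim 2 unless stated.

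- **Selection (Sample).** The Hot Spot report flags veterans with at least one admission and/or at least two "ED visits in the past quarter of the fiscal year". From these, the trial takes patients who "have not been engaged in either primary care or mental health during the quarter that they were flagged on the report".
- **Outcomes (Outcome measurement).** The first Effectiveness measure is the "number of outpatient visits in primary and specialty visits for mental health/SUD care". Additional patient-level outcomes include "rates of suicide screening and hospitalizations and emergency department visits".
- **Order of conditions (abstract, Methods; Design).** Sites follow one sequence, "beginning with Audit and Feedback (low-intensity) and then switching to Implementation Facilitation (high-intensity) after 6 months", and "sites will spend twice as long in HI than LI".
- **Overlap (Analysis).** "Individual patients may be observed in both LI and HI"; others appear at one stage only. The share in each group is not given.
- **Model (Analysis).** A GLMM for each outcome has patient and site random effects, demographics, site volume per provider and staffing changes. The following paragraph, which opens with Reach, recognises that a patient's care-seeking changes over time and can confound beyond what site randomisation controls. Its remedy is two offsets, one for the length of opportunity in each condition and one for the patient's number of encounters.

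**The concern.** A patient chosen because one quarter was extreme will tend to look less extreme later if part of that extreme was temporary. Here the extreme is high acute use together with no outpatient engagement, so the drift is towards fewer admissions and ED visits and more outpatient visits. That is also the direction the trial hypothesises for HI. Because HI follows LI at every site, anyone seen in both conditions contributes HI time that is further from the flag.

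The remedy in the Analysis section deals with how much exposure a patient had to a condition. It does not deal with how long ago the patient was selected. At stake is whether a difference in service use can be read as an effect of the implementation strategy.

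**Working it through.** The protocol has no figure of its own on this point. Its one calculated figure nearby, 227 to 278 patients, concerns a binomial outcome such as reach. It cannot be reproduced uniquely, because the baseline proportion is not given, and nothing below depends on it.

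**Step 1. Time since flag in each condition.** LI lasts 6 months, or 2 quarters. HI lasts twice as long, or 4 quarters. Number the site's quarters 1-2 (LI) and 3-6 (HI), and leave the flag quarter out.

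- Closed cohort flagged in quarter 0: LI mean (1+2)/2 = 1.5 quarters; HI mean (3+4+5+6)/4 = 4.5 quarters.
- Equal numbers flagged in each of quarters 0 to 5 and followed to quarter 6: LI (1+2+1)/3 = 1.33. HI (18+14+10+6+3+1)/18 = 52/18 = 2.89.
- The same entry, but at most two quarters after the flag: LI 4/3 = 1.33; HI (2+3+3+3+1)/8 = 12/8 = 1.50. Those who cross (flagged in quarter 1) still have LI at lag 1 and HI at lag 2.

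The gap has the same sign at every site, so randomising the switch date cannot balance it.

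**Step 2. When the gap matters.** Suppose the temporary part of a patient's log-rate deviates by d in the flag quarter and has serial correlation ρ. The expected deviation k quarters later is d·ρ^k. Average share remaining in the closed cohort:

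| ρ | LI, lags 1-2 | HI, lags 3-6 | difference |
|---|---|---|---|
| 0.3 | 0.195 | 0.010 | 0.185 |
| 0.7 | 0.595 | 0.217 | 0.378 |
| 0.9 | 0.855 | 0.627 | 0.228 |

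With ρ = 0, or with a wholly permanent deviation, LI and HI are equal and there is no bias. The 0.7 in the Sample section is the correlation between LI and HI periods used in the power scenarios, not a value for service use.

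**Step 3. Simulations with no strategy effect.** All rates and variances are assumed. Non-engagement is read as zero visits, although the wording of that criterion is ambiguous.

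*Set-up A:* log-normal quarterly rates (acute log-mean -1.5, SD 1.0; visits log-mean 0.3, SD 1.2), ρ from 0.3 to 0.7, rolling entry at the first quarter with at least one acute event and no visits, flag quarter excluded.

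*Set-up B:* 0.1 admissions, 0.3 ED visits and 1 or 2 outpatient visits per quarter, total log-SD about 1, ρ from 0.3 to 0.9 or fully stable rates, the protocol's flag rule.

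| Scenario | HI/LI outpatient | HI/LI acute |
|---|---|---|
| A, followed to end, all patients | 1.19-1.42 | 0.83-0.91 |
| A, followed to end, seen in both phases | 1.27-1.60 | 0.79-0.86 |
| A, two quarters after flag, entry from quarter 0 | 1.04-1.10 | 0.92-0.98 |
| A, two quarters after flag, entry only once LI starts | 1.16-1.23 | 0.86-0.93 |
| B, closed cohort, serially correlated rates | 1.06-1.43 | 0.70-0.93 |
| B, closed cohort, stable rates | 1.00 | 1.00 |
| B, flagged in LI, flag quarter counted | 2.9-4.0 | 0.37-0.53 |

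The last row holds even with stable rates. A further set of runs with the flag quarter excluded gave 1.05-1.55 and 0.82-0.96.

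False-positive rates came from set-up B with ρ = 0.7, N = 585, 7 sites, one site starting per quarter and 250 trials per scenario. The model was a Poisson regression with site effects and patient-clustered standard errors, standing in for the GLMM. In the closed cohort the null was rejected in favour of HI in 64% (outpatient) and 84% (acute) of trials. Calendar-quarter effects reduced this to 32% and 51%. With rolling entry, follow-up to the end and calendar effects, the rates were 10% and 25%. In the closed cohort with stable rates, rejection in either direction was 4% to 6%.

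**Step 4. What removes it.** A categorical time-since-flag term brought the further runs to 0.99-1.10 and 0.91-1.00 when patients had no permanent differences. With half the rate variance permanent it left 1.08-1.14 and 0.83-0.88, because more severe patients are flagged first. In set-up B with stable rates, rolling entry and calendar effects, adding that term alone moved the ratios further from 1 (1.04 to 1.10; 0.89 to 0.79). Adding flag-quarter cohort as well brought nearly all scenarios to 0.97-1.05. The phase effect stays estimable because it is a step at the switch, not a sum of a cohort effect and a lag effect.

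**The case against.** The strongest reply is that this is a condensed article. Outcome windows, handling of the flag quarter and the full list of model terms commonly sit in a full protocol or analysis plan, and the figure on the analytic approach is not available here. That stands as far as it goes: a missing time-since-flag term would not be a fault by itself. But the article does name a patient-level time problem and does choose a remedy, and that remedy answers a different problem. Under the design and model as stated, the exposure remains.

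Three further objections stand and limit the point:

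- Patients only *may* be seen in both conditions. Hot Spot data refresh nightly and HI is the longer phase, so many patients may be newly flagged in HI, which dilutes the contrast.
- Peer contact lasts up to six months. If outcome follow-up were capped likewise, the drift would be smaller overall. In set-up A it persists in those who cross (1.25-1.36 outpatient, 0.87-0.91 acute). A cap also does not remove the effect of severe patients being flagged first.
- Calendar terms reduce the false-positive rate, though they do not restore it.

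A reader might infer that acute use is bound to fall and outpatient use bound to rise, so that HI must look better whatever the truth. The documents do not support that. They give no serial correlation for service use, and a closed cohort with stable rates and the flag quarter excluded shows no bias.

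**Conclusion.** The point holds in a conditional form. For primary care and mental health/SUD visits, hospitalisations and ED visits, the HI-versus-LI contrast is exposed to regression to the mean in favour of HI. The switch-date randomisation, calendar-period terms and the stated offsets do not remove it.

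The null ratios of roughly 1.05-1.55 (outpatient) and 0.82-0.96 (acute) are illustrative. They rest on assumed rates, variances and serial correlation, and on leaving the flag quarter out. Counting that quarter would make matters much worse.

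It would be wrong to extend this to the whole trial. Reach (the power example), adoption and fidelity are not affected. Whole Health engagement, HUD-VASH exits and suicide screening are not selection variables. The service-use outcomes are nevertheless part of the hypothesis that HI does better on all RE-AIM outcomes, so the handling should be fixed before outcome data are analysed.

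**What to change.** In every service-use GLMM:

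1. Exclude the flag quarter from outcome time.
2. Classify each patient-quarter by the phase actually in force at the site.
3. Add a categorical time-since-flag term and an adjustment for flag-quarter cohort, meaning the site-relative quarter in which the patient was flagged. Both are needed.
4. Do not apply the encounter offset to outpatient-visit outcomes. It would overlap the outcome and could absorb a real effect.

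A fixed post-flag window analysed by phase at flag can serve as a sensitivity analysis only. With two LI quarters, about 45-48% of patients flagged in LI in the set-up A runs had their first post-flag quarter wholly in HI, so counting them as LI would dilute a true effect.

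**Cost.** Analysis wording only, since the Hot Spot reports already identify the flag quarter. The models gain a few terms and the phase effect loses some precision, more so if follow-up per patient is short.
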